### Eligibility criteria

To be included in this study, subjects must: (1) provide informed consent to participate in the study; (2) be between 18–60 years old, regardless of gender; (3) have a diagnosis of muscular TMD pain according to IA and IB, Axis I of Research Diagnostic Criteria for Temporomandibular Disorders (RDC/TMD); (4) have a visual analog scale (VAS) pain score of 4 or greater, present regularly for 6 months or longer; (5) have a State-Trait Anxiety Inventory (STAI) score of more than 42.

Subjects will be excluded from this study if they (1) are pregnant; (2) have contraindications to tDCS, such as metal implants on the head or implanted brain devices; (3) have a history of alcohol or drug abuse within the past 6 months as self-reported; (4) have used carbamazepine within the past 6 months as self-reported; (5) have a history of epilepsy, stroke, moderate-to-severe traumatic brain injury, or severe migraines; (6) have a history of neurosurgery as self-reported; (7) have a history of temporomandibular joint problems such as disc displacement, arthralgia, osteoarthritis, or osteoarthrosis (Axes I, II, and III diagnosis from RDC/TMD); (8) have a major psychiatric disorder such as schizophrenia or bipolar disorder; (9) have had any other previously diagnosed disorder that has pain symptoms similar to muscle TMD, such as fibromyalgia.

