### Sample size

Following IMMPACT (Initiative on Methods, Measurement, and Pain Assessment in Clinical Trial) [25] recommendations for clinical trials involving chronic pain, we considered our primary outcome measure to be pain intensity changes, assessed through a VAS. We achieved a sample size of 15 subjects (G*Power 3.1), considering a reduction of 50 % (effect size of 0.5), a study power of 80 %, an alpha value of 5 % (*P* < 0.05), and six measures (three pre- and post-measures) on three intervention groups (placebo, and tDCS 1 mA and 2 mA).

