### Allocation of interventions

Subjects will be consecutively randomized in order of the interventions using the tool from randomization.com (DallalGE, http://www.randomization.com). This study will use the second generation suggested for crossover studies. Only the investigators assigned to apply tDCS will have access to the randomized list. This list will be opened only when all data are available and analyzed, unless a subject has a side effect that justifies the interruption of the procedure.

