### Statistical methods

The data will be recorded and analyzed by a blinded biostatistician. First, a descriptive analysis of variables will be performed. Data distribution will be analyzed using the Shapiro-Wilk test. To check carryover effects between sessions, we will carry out a *t*-test or a Wilcoxon rank sum, depending on the normal distribution.

Outcome measures will be compared both between and within groups considering pre- and post-interventions with repeated measures analysis of variance or nonparametric correspondence tests (Friedmann and Mann–Whitney tests). Clinical data will be correlated to EEG data through correlation tests (Spearman or Pearson). Significance will be established at an alpha value of 5 %, with a study power of 80 %. All data will be analyzed with intention-to-treat.

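### The stated analysis has no period term although treatment order is randomised, and its named tests cannot use a patient with a missed session despite the intention-to-treat claim

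*Protocol article*

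**What the plan says.** Study design describes one group that receives all three interventions in random order. Allocation of interventions adds: "Subjects will be consecutively randomized in order of the interventions using the tool from randomization.com". It then refers to the tool's scheme for crossover studies, but gives no set of orders, no block size and no statement on balance over periods.

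Statistical methods gives the comparison: "Outcome measures will be compared both between and within groups considering pre- and post-interventions with repeated measures analysis of variance", with Friedman and Mann–Whitney tests as alternatives. Study variables lists 1 mA, 2 mA and sham as the only independent variables. The one step related to order is a separate carryover test (t-test or Wilcoxon rank sum). The analysis set is fixed by "All data will be analyzed with intention-to-treat".

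The primary outcome (Outcomes) is diary VAS, averaged over one week before the first intervention and over the week after each session. Table 1 and the VAS section also record VAS immediately before and after each session.

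**The concern.** In a crossover trial the treatment contrast is made within patients across weeks, so any common week-to-week change in pain is a nuisance that the model should remove. Such a change is plausible here. Entry requires patients to "have a visual analog scale (VAS) pain score of 4 or greater" and to have raised anxiety, so some regression towards usual levels can be expected, and patients become used to the procedure over three weekly visits. The washout and the carryover test do not adjust the treatment contrast for a week effect.

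At stake is precision in a trial of 15 patients planned at 80 % power and, in the single allocation that is realised, a possible chance shift of the active-versus-sham contrast. Separately, classical repeated-measures ANOVA and the Friedman test work on complete blocks, so one missed session removes all of that patient's data, 1/15 = 6.7 % of the total.

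**Working it through.** **The plan's own figure.** Inputs from Sample size: "six measures (three pre- and post-measures) on three intervention groups", effect size 0.5, 80 % power, alpha 5 %, N = 15. The correlation among measures (rho) is not stated. With λ = f²·N·m/(1 − rho):

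- Group-by-time interaction, 3 groups, m = 6, rho = 0: λ = 0.25 × 15 × 6 = 22.5 on 10 and 60 df; power 0.88, and N = 15 is the smallest multiple of three that reaches 80 %.
- One group, m = 3, rho = 0: λ = 0.25 × 15 × 3 = 11.25 on 2 and 28 df; power 0.82, smallest N = 15.

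So 15 reproduces, but only with a correlation that the protocol does not give. Sample size mentions neither period nor dropout.

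**Balance.** Three treatments have 3! = 6 orders. 15/6 = 2.5, so equal numbers per order are impossible. What matters for a period effect is treatment-by-period balance, and 15/3 = 5 is attainable. By chance it arises in 0.36 % of allocations if each order is drawn independently (exact enumeration), and in 10 % with permuted blocks of six (2 of the 20 possible half-blocks).

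**Size of imbalance.** Per patient, the variance of the period difference between two treatments is (4 × 1 + 2 × 4)/6 = 2. Over 15 independently drawn patients the mean difference has SD √(2/15) = 0.37 periods, and it exceeds 0.5 in about 17 % of allocations. With blocks of six the maximum is 4/15 = 0.27.

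**Cost with perfect balance.** Assume residual SD 1 cm, true effect 1 cm, linear drift b cm/week, and post-session values compared as levels. The true SE of a contrast is √(2/15) = 0.365.

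- Without period, drift adds 15 × 2 × b² = 30b² to a residual sum of squares on 28 df. The expected residual variance is 1 + 30b²/28.
- b = 0.5: 1 + 7.5/28 = 1.27. The estimated SE is 0.365 × √1.27 = 0.411, the difference needed for significance is 2.048 × 0.411 = 0.84 cm, and power ≈ P(Z > (0.84 − 1)/0.365) ≈ 67 %.
- b = 1: 1 + 30/28 = 2.07. The SE is 0.526, the difference needed is 1.08 cm, and power ≈ 42 %.
- With period (26 df): the difference needed is 2.056 × 0.365 = 0.75 cm and power ≈ 75 % at any b.
- Without period and b = 0: 2.048 × 0.365 = 0.75 cm and power ≈ 75 to 76 %.

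**Cost with independently drawn orders** (simulation, same assumptions; ranges are over separate runs):

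| Drift | Power without period | Power with period |
|---|---|---|
| 0 | 75–77 % | 71–72 % |
| 0.5 cm/week | 64–66 % | 70–72 % |
| 1 cm/week | 44–47 % | 71–73 % |

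**Type I error without period.** Averaged over independent draws it is about 4 to 6 %. With blocks of six or balanced periods, and drift of 0.5 to 1 cm/week, it falls to about 3 % or less, so the test is conservative. Within the 17 % most unbalanced independent allocations it is about 10 to 11 % at 0.5 cm/week and 18 to 19 % at 1 cm/week.

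**Missed sessions.** Starting from 80 % power with 15 patients, restriction to completers gives about 77 % with 14, 73 % with 13 and 69 % with 12.

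**The case against.** The strongest reply is that the planned comparison may already remove the drift. VAS is taken before and after each session on the same day, so a slow change in level enters both values and cancels. If each diary week is compared with the preceding week, a linear trend adds the same constant to every change and also cancels from treatment contrasts. This stands, and it limits the point: the power figures apply only if post-session weeks are compared as levels or against the one pre-trial week. That week is constant within a patient, so it cannot adjust a within-patient contrast. Outcomes and the VAS section leave open which comparison is primary. A non-linear drift, such as settling after the first session, would not cancel from week-on-week changes.

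It is also fair that the drift sizes have no source in the protocol, and that the 7-day diary after screening should absorb part of any regression to the mean before the first session.

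Three stronger readings are tempting and not supported:

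- A reader might infer that 15 patients cannot be balanced. That is true only per order, and the protocol does not commit to six orders.
- A reader might infer that the false-positive rate is inflated. On average it is not. The 10 to 19 % figures belong to the most unbalanced allocations under independent draws; under blocks of six no allocation is that unbalanced.
- A reader might infer that the plan drops incomplete patients. No such rule is stated; it is a property of the named tests and arises only if a session is missed. Detailed missing-data rules may sit in a fuller document.

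**Conclusion.** The point holds as a limited one that is worth acting on. The protocol fixes an analysis on treatment and pre/post only, although order is what it randomises, and the text does not secure balance over periods. The main harm is lost precision, not false positives. Under the assumptions stated (residual SD 1 cm, effect 1 cm, levels compared), leaving period out costs about 6 to 8 points of power at 0.5 cm/week and about 25 to 33 points at 1 cm/week, over the allocation schemes examined. Balancing periods does not remove this loss, because the drift still sits in the residual; it removes only the chance bias. If drift is absent or cancels, the harm is nil. The conflict between complete-block tests and the intention-to-treat sentence is real but conditional: about 3 points of power for the first lost patient.

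**What to change.** Make the primary analysis a linear mixed model with treatment and period as fixed effects, patient as random effect and the pre-intervention value as covariate, fitted to all available sessions. State which pre-intervention value is meant for the diary outcome. Base claims on the active-versus-sham contrasts, not on pre/post tests within an intervention. Patients with a missed session then contribute what they have, which brings the analysis into line with the intention-to-treat sentence.

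The cost is a change of wording, two error degrees of freedom (28 to 26) and, if there is no drift, a power loss of about 0 to 5 points: almost none with balanced periods, most with independently drawn orders.

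Changing the randomisation list is optional. Two full sets of the six orders (12 patients, 4 per treatment-period cell) plus one three-order Latin square (1 more per cell) would give 5 per cell. Recruitment is under way, so this should be considered only for unused entries and only where concealment is not compromised. The period term is worth having either way.

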### Outcomes

The primary outcome of this study will be the extent to which this method will change baseline pain intensity (VAS). The subjects will record their experience on a daily basis in a pain diary. A weekly response average will be calculated before the first intervention and after each session. The averages will be used to compare the VAS values before and after each intervention. A decrease of 50 % will be considered a satisfactory clinical improvement.

Secondary outcomes will be the degree of change from baseline in power density of alpha and theta EEG bands. Other outcome measures will be pain pressure threshold (PPT), mechanical pain thresholds (MPTs), and STAI. Increase in PPT and mechanical thresholds indicate an improvement in subject pain condition; a decrease in STAI indicates a better emotional state.

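### The sham comparison is planned but not made decisive: the only primary pain comparison that Outcomes names is before versus after each intervention, which cannot separate a tDCS effect from a response shared with sham

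*Protocol article*

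**What the plan says.** The main objective (Aims) is whether cathodal tDCS relieves muscular TMD pain. Every patient receives 1 mA, 2 mA and sham in random order. None of the five numbered aims names a comparison with sham; the only contrast between conditions named there is 1 mA against 2 mA.

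Outcomes makes change from baseline VAS the primary outcome, measured by weekly diary averages, and says how they are used: "The averages will be used to compare the VAS values before and after each intervention". It then counts a 50 % decrease as satisfactory, without reference to sham. The VAS section adds that scores taken before and after each session will serve to verify the treatment effect.

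Statistical methods is wider: "Outcome measures will be compared both between and within groups considering pre- and post-interventions with repeated measures analysis of variance", or nonparametric counterparts. Alpha appears once: "Significance will be established at an alpha value of 5" %. It is not allocated across tests, and no comparison is identified as the one that decides.

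Other sections point towards a controlled comparison. Study design calls the trial controlled, Study variables lists sham as an independent variable, and Sample size refers to "six measures (three pre- and post-measures) on three intervention groups (placebo, and tDCS 1 mA and 2 mA").

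**The concern.** A fall in pain from before to after an active session contains any effect of stimulation, but also placebo response, natural course and whatever regression to the mean remains after entry on VAS of 4 or more. The sham session carries the same components. Only the difference in change between active and sham removes them, and the sham period is in the design for that purpose.

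Outcomes does not merely leave detail to a later document. It names a primary comparison, and that comparison is uncontrolled. An analysis plan that followed it could report that 1 mA or 2 mA reduced pain when neither did better than sham. An analysis plan that relied on Statistical methods could make the controlled comparison primary. Both would comply with the article, and they can give opposite answers from the same data.

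**Working it through.** **1. The plan's own figure.** Sample size states "We achieved a sample size of 15 subjects (G*Power 3.1"), "considering a reduction of 50 % (effect size of 0.5"), with "a study power of 80 %, an alpha value of 5" %. The test and the correlation between measures are not given. For the within-between interaction in a repeated measures ANOVA, λ = f²·N·m/(1−ρ).

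- f = 0.5, N = 15, m = 2 (pre, post), ρ = 0.5: λ = 0.25 × 15 × 2 / 0.5 = 15. On 2 and 12 df the power is 0.87, and 15 is the smallest multiple of three that reaches 80 %.
- m = 6, ρ = 0: λ = 0.25 × 15 × 6 / 1 = 22.5. Power is 0.88, and the smallest N is again 15.
- m = 6, ρ = 0.5: the interaction needs 9, the within test 9 and the between test 27.

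So 15 can be reached from a group-by-time test, but only under choices the text does not state. Sample size therefore does not reveal which comparison was meant to decide.

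**2. Inputs for the check.** From the document: n = 15, three conditions per patient, alpha 5 %. Assumed: two-sided tests; no true active-sham difference; the same mean fall δ in all three conditions, in SDs of the pre-to-post change; correlation of changes between conditions from 0 to 0.5.

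**3. One active condition, before versus after.** With 14 df the critical t is 2.145, so a mean fall above 2.145/√15 = 0.55 SD is significant. The noncentrality is δ√15.

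| Shared fall δ | δ√15 | One given active condition significant |
|---|---|---|
| 0.25 SD | 0.97 | 15 % |
| 0.5 SD | 1.94 | 44 % |
| 0.75 SD | 2.90 | 77 % |

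**4. At least one of the two active conditions.** If the changes are independent this is 1 − (1 − p)²: 1 − 0.853² = 27 %, 1 − 0.562² = 68 % and 1 − 0.229² = 95 %. By simulation with correlation 0.5 it is 24 %, 61 % and 90 %. The simulated ranges over correlations 0.5 to 0 are:

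| Shared fall δ | At least one active significant | Condition-by-time F test |
|---|---|---|
| 0.25 SD | 24–27 % | about 5 % |
| 0.5 SD | 61–69 % | about 5 % |
| 0.75 SD | 90–95 % | about 5 % |

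The last column does not depend on δ, because a shared fall cancels between conditions.

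**5. Setting separate P values side by side does not help.** At δ = 0.5 SD, an active condition is significant while sham is not in about 26–39 % of these null trials.

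**6. The controlled contrasts.** One active-versus-sham paired contrast at two-sided 5 % rejects in about 5 % of null trials. Either of two unadjusted contrasts rejects in about 9 %. If they were independent it would be 1 − 0.95² = 9.75 %, and the shared sham period lowers it slightly.

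**The case against.** The strongest reply is that a controlled comparison is already planned. Statistical methods covers between- as well as within-group comparison, sham is a level of the independent variable, and the natural reading of a repeated measures ANOVA on pre and post data is condition by time, which holds its level. The rates in the second table are rates of within-condition significance. They become false claims of analgesia only if the between-condition result is set aside, and nothing in the protocol directs that. This stands, and it limits the point to which comparison decides.

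A reader might infer more than the text supports:

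- **That pain is tested only before versus after.** It is not; the sentence in Statistical methods plans both kinds of comparison.
- **That each test is run at its own 5 %.** The document states one alpha and is silent on its allocation.
- **That familywise error is about 12.5 %.** That figure belongs to three ungated pairwise tests between conditions. The plan names omnibus tests and does not describe such a procedure.
- **That regression to the mean passes in full into the before-after change.** The baseline is a separate 7-day diary average collected after the screening visit, so much of the regression would fall within the baseline week. Placebo response and natural course are not removed in this way.
- **That the treatment later offered to participants will be chosen on within-condition P values.** Ethical aspects refers only to the best protocol found and does not say how it is picked.

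It is also fair to say that exact model terms and a testing hierarchy can wait for an analysis plan. What cannot be deferred in that way is a primary comparison that Outcomes already names without sham.

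**Conclusion.** The point holds in this limited form. The article names an uncontrolled before-after comparison and an uncontrolled 50 % threshold for the primary outcome, plans a controlled comparison elsewhere, and does not say which one carries the conclusion. If the before-after comparison is used, a shared fall of 0.5 SD gives about a 61–69 % chance that at least one active intensity appears effective when neither differs from sham. The controlled test would give about 5 %.

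The size rests on assumed shared falls and correlations, since the document gives no SD, correlation or expected sham response. At a fall of 0.25 SD the figure is 24–27 %, still about five times the nominal level. With no shared fall at all the problem disappears, but a sham-controlled pain trial cannot presume that. Because the main conclusion depends on the choice, it should be settled before the data are analysed.

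**What to change.** State the following in both Outcomes and Statistical methods. The primary test is the difference between each active intensity and sham in change of the weekly diary VAS average, estimated by the within-patient crossover comparison. The overall two-sided 5 % covers the two active-versus-sham contrasts. Changes within an intervention, and the proportion with a 50 % decrease, are reported descriptively or compared with sham. Naming the diary average matters, because the VAS section also uses session scores to verify the effect.

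Model terms and the method of alpha control can be left to the analysis plan.

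The change needs no new data or visits. The cost is power per contrast. With the simplest split, 2.5 % for each contrast, the critical t on 14 df rises from 2.145 to 2.510. For a true active-sham difference of 0.8 SD of the paired difference, power falls from 82 % to 72 %; at 1.0 SD it falls from 95 % to 90 %. A stepwise procedure loses less, and a fixed order of testing loses nothing for the contrast placed first.

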## Methods

### Study design

This is a randomized, controlled crossover double blind study with one group undergoing three different interventions. Treatment order will be determined randomly. The CONSORT guidelines from 2010 to clinical trials will be used to guide the procedures [20].

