### Intervention C

This will be the sham intervention. Stimulation electrodes will be placed at the same areas as for interventions A and B, but the current will be applied only for the first 30 seconds, after which it will be reduced gradually until it reaches zero. This method has been shown to be effective in previous studies [21].

In all the intervention groups, tDCS will be applied using 35 cm^2^ (5×7 cm) sponge electrodes soaked in saline solution (140mMolNaCl, water dissolved in Mille-Q). Anodal and cathodal electrodes will be connected in the tDCSdevice (Soterix Medical 1 × 1 tDCS 1300A, USA). Two 9-V batteries will deliver current.

All subjects will receive only one stimulation session for each type of intervention (IA, IB and IC), for a total of three sessions. After each tDCS session, the subject will complete a questionnaire to record any adverse affects. A trained researcher ([name]) will perform each procedure. One researcher who is responsible for the general supervision ([name]) during testing will hold the randomization list, and only the clinician responsible for the tDCS stimulation will know which intervention group is being applied. All clinical and neurological assessments will be performed at the Functional Electrostimulation Laboratory at Federal University of Bahia (Salvador, Brazil).

As this is a crossover study with only four weekly sessions, we believe that there will not be a compliance problem. Furthermore, since side effects are minimal, there is a low risk of dropouts due to this reason.

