### Control group

As a crossover study, each subject will be his/her own control. This choice is supported by studies that evaluated motor cortical excitability with transcranial magnetic stimulation (TMS) and found that a single tDCS session is able to modify cortical excitability for up to 1.5 hours after the end of stimulation. This suggests that a carryover effect is not an issue [22, 23]. Furthermore, EEG data is one of our outcome measures, and individual characteristics are crucial in this analysis [24], being minimized by a crossover design.

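### In the non-parametric branch, the two-sample tests named (Mann–Whitney, Wilcoxon rank sum) assume independent samples, although the pre/post, pairwise-treatment and between-session comparisons are all made within the same 15 subjects

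*Protocol article*

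**What the plan says.** Study design describes a "randomized, controlled crossover double blind study with one group undergoing three different interventions". The Intervention C section confirms it: "All subjects will receive only one stimulation session for each type of intervention (IA, IB and IC), for a total of three sessions". Control group gives the reason for the design: "As a crossover study, each subject will be his/her own control".

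Statistical methods then sets out the analysis. Outcomes are to be compared both between and within groups, taking pre- and post-intervention values into account, with "repeated measures analysis of variance or nonparametric correspondence tests (Friedmann and Mann–Whitney tests"). Carryover between sessions is to be checked with a t-test or "a Wilcoxon rank sum, depending on the normal distribution". The section on the VAS for pain says that each week's diary average will serve for the carryover check. A Shapiro–Wilk test of the distribution comes before these steps. No paired two-sample rank test is named anywhere in the article.

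**The concern.** Mann–Whitney and the Wilcoxon rank-sum test are the same procedure, and it assumes two independent samples. This trial has no independent treatment samples. Post against pre, 1 mA against sham, 2 mA against sham, 1 mA against 2 mA, and one week's diary mean against another week's all compare the same people with themselves.

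Friedman can say whether the three interventions differ somewhere, but not which. The Aims section wants 1 mA compared with 2 mA, and Technical and scientific resources speaks of finding the most effective protocol. In the non-parametric branch, Mann–Whitney is the only named test that could answer those pairwise questions.

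An unpaired test on positively correlated pairs uses too large a variance, so its p-values are too large. A real analgesic difference could go undetected. A real carryover could also pass as absent, and the absence of carryover is what the crossover relies on.

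**Working it through.** **The plan's own figure.** Sample size states "We achieved a sample size of 15 subjects (G*Power 3.1"), "considering a reduction of 50 % (effect size of 0.5), a study power of 80" %. For repeated measures ANOVA with k groups and m measures, the interaction has noncentrality λ = f²·N·m/(1−ρ) with (k−1)(m−1) and (N−k)(m−1) degrees of freedom. The correlation ρ is not stated.

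- f = 0.5, k = 3, m = 6, ρ = 0: N = 13 gives λ = 0.25 × 13 × 6 = 19.5 and power 0.80. Rounding up to three equal groups gives 15, with power 0.88.
- One group, m = 3, ρ = 0, within-subject effect: N = 15 gives λ = 0.25 × 15 × 3 = 11.25 and power 0.82.
- k = 3, m = 6, ρ = 0.5: the interaction needs only 8, so this does not reproduce 15.

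So 15 can be reached, but only with inputs that are not stated. Each route is a repeated measures ANOVA calculation and none uses Mann–Whitney. The point here does not depend on the sample size being wrong.

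**Why the unpaired test is conservative.** For two measurements on the same n subjects with common SD σ and correlation ρ, the mean difference has variance 2σ²(1−ρ)/n. An unpaired test works as if it were 2σ²/n. In large samples its true two-sided level is therefore about 2Φ(−1.96/√(1−ρ)):

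- ρ = 0.3: 1.96/0.837 = 2.34, level about 1.9 %
- ρ = 0.5: 1.96/0.707 = 2.77, level about 0.6 %

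**Simulation at n = 15.** Inputs: bivariate normal pairs, 20,000 runs per cell, two-sided 5 % (sidedness is not stated in the article), exact critical values U ≤ 64 and W ≤ 25. The correlations and the shifts in SD units are assumptions. The 0.5 SD shift is not the same quantity as the effect size of 0.5 entered in G*Power.

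| ρ | Type I error, Mann–Whitney | Type I error, signed-rank | Power at 0.5 SD, Mann–Whitney vs signed-rank | Power at 0.8 SD, Mann–Whitney vs signed-rank |
|---|---|---|---|---|
| 0 | 4.4 % | 4.8 % | 24 % vs 24 % | 52 % vs 51 % |
| 0.3 | 1.9 % | 4.7 % | 20 % vs 31 % | 53 % vs 66 % |
| 0.5 | 0.7 % | 4.7 % | 17 % vs 41 % | 54 % vs 80 % |
| 0.7 | 0.1 % | 4.8 % | 14 % vs 61 % | 56 % vs 95 % |

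To match the signed-rank test on 15 subjects at a 0.8 SD shift, Mann–Whitney would need about 19 subjects at ρ = 0.3, 24 at 0.5 and 30 at 0.7.

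**Change scores.** Suppose each subject has a stable level plus independent errors of variance σₑ², and no patient-specific response.

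- *Separate baseline at each session.* The subject's level cancels from each change and no error is shared, so the changes under two treatments have correlation 0. At a shift of 0.8 SD of the change, power is 52 % (Mann–Whitney) and 51 % (signed-rank), so nothing is lost.
- *One common baseline.* Two changes share one error term. The covariance is σₑ² and each variance is 2σₑ², so the correlation is 0.5. Power is then 53 % against 79 %, in line with the ρ = 0.5 row.

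Both situations are possible here. Table 1 has a pre-stimulation VAS at every session, while the Outcomes section describes one diary average before the first intervention and one after each session.

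**The case against.** The strongest defence is one of scope. The first-named analysis is repeated measures ANOVA and the first-named rank test is Friedman. Both block on the subject, so the overall three-treatment comparison stays paired in either branch. That stands, and it limits the point to the pairwise, pre/post and carryover tests of the non-parametric branch.

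Four further objections have weight:

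- A rank-sum test is a legitimate carryover check when it compares randomised sequence groups, which are independent. The article, however, speaks of carryover between sessions and of weekly averages, which points to within-subject comparisons. As worded the test does not fit, but a different comparison could make it fit.
- The power figures come from normal data, for which Shapiro–Wilk would send only about 5 % of analyses to the rank tests. They illustrate the loss and do not forecast it.
- For between-treatment comparisons of change from separate session baselines, the loss can vanish, as shown above.
- An article condenses, and the test that follows Friedman is often settled in the analysis plan. This excuses silence. It does not excuse naming a test that does not fit the design.

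A reader might also infer more than the text supports:

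- *That the whole rank-based analysis discards the crossover.* Friedman does not.
- *That Friedman would be run on six raw pre and post values and so answer the wrong question.* The six measures appear under Sample size, and six data collection points under Data collection procedure. Statistical methods does not say what Friedman is applied to.
- *That false positive claims of efficacy would follow.* With positive correlation the error runs the other way.
- *That choosing the branch by Shapiro–Wilk is part of this fault.* That is a separate methodological preference.

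**Conclusion.** The point holds in a limited form. The two-sample rank tests named do not suit comparisons within one group of 15 subjects, and the mismatch can be read directly from the article. It matters only if the non-parametric branch is taken, and then only for the pairwise, pre/post and carryover tests.

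Where the compared values are positively correlated, Mann–Whitney runs at a true level of about 0.1–1.9 % instead of 5 % for correlations of 0.3 to 0.7. At a 0.8 SD shift it gives up between about 13 percentage points of power (66 − 53) and about 39 (95 − 56). At 0.5 SD the gap runs from about 11 points (31 − 20) to about 47 (61 − 14), though there the paired test too stays below the planned 80 %. These sizes rest on normal data, an assumed correlation and assumed shifts. Near zero correlation the loss disappears, including for change scores with separate baselines and no patient-specific response.

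The practical risk is a missed effect or a carryover check that reassures too easily. This is a wording correction that should be made before analysis; it does not invalidate the trial's main parametric analysis.

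**What to change.** Change two sentences in Statistical methods.

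1. *Outcomes, non-parametric branch.* Run Friedman on each subject's three post-minus-pre changes. Replace Mann–Whitney with the Wilcoxon signed-rank test on within-subject differences: post against pre within an intervention, and pairwise differences in change between interventions.
2. *Carryover.* If the comparison is between sessions, use a paired t-test or a signed-rank test on the weekly diary averages. Keep the rank-sum test only if the text says that randomised sequence groups are being compared.

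No extra data, visits or subjects are needed. The cost is the rewording and its entry in the analysis plan before the randomisation list is opened.
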